#### Evidence of selection bias

Since this is a pilot trial with only four clusters randomised, it is likely that there will be some imbalance between participants in each of the treatment arms on one or more baseline characteristics. Baseline comparisons will be carried out to detect any substantial differences between participants recruited from the control and intervention arms. This will be done by scrutinising the baseline table for any serious imbalances in observable baseline variables and the trends of the imbalance if any. The recruitment rates will also be estimated and compared between the control and intervention arms. We will examine the size of any imbalances and decide if there is evidence of systematic selection bias in the types of patients being recruited in control versus intervention arms. Any systematic imbalance in the sense that one arm is consistently favoured by the imbalances may not reflect chance alone and may suggest selection bias.

#### Explore generalisability of the sample

Anonymised data on key baseline characteristics (age, gender and index of multiple deprivation (from post-codes)) of those who are invited but who do not participate will be compared with those who do participate. Key baseline characteristics will be compared between those participants followed up and those lost to follow-up at each time-point. Key characteristics of the participants recruited using each recruitment method will be reported. Delays in return of questionnaires (>35 days from initial mailing date) will also be compared between the two arms.

#### Analyses of clinical outcomes

Analyses will be conducted for the clinical outcomes, but this will be treated as exploratory and will be mainly descriptive. A baseline table (descriptive statistics and frequencies) will compare the demographic and clinical characteristics (gender, age, education, employment status, pain interference with performance at work, type of accommodation, health literacy, physical health (SF-36v2 PCS) and mental health (SF-36v2 MCS), pain location, physical function, pain duration, baseline risk of persistent problems, comorbidities, pain self-efficacy, understanding of the condition, experience of care and convenience and accessibility of service) between the two arms. Since the baseline assessment for the clinical characteristics will be completed, for many patients, after their initial consultation about their musculoskeletal problem, there could be implications on evaluation and interpretation of these measures as they may not be ‘true baseline’ but rather possible ‘outcomes’ at the first time-point. All continuous variables will be summarised using mean, standard deviation, median and interquartile range as appropriate. The frequency and percentages of observed levels will be reported for all categorical measures.

As this is a pilot trial, no emphasis will be put on the *p* values for any inferential statistical tests conducted. A mixed effect model, which allows all available data at all the four time-points to be used and account for missing data and clustering effect, will be used to estimate a two-sided 95 % CI to show a credible range for the true difference in the SF-36v2 PCS subscale between intervention and the control arms. The model will be adjusted for key patient-level baseline characteristics (age, area level deprivation and widespread pain (from manikin data)) and a random effect for the GP practices and will include a treatment-by-time interaction to obtain the estimates of treatment effect (and 95% CI) at each follow-up visit (2, 6 and 12 months). Analyses of the secondary outcomes will be performed similarly.

Further analysis will descriptively compare the baseline characteristics and key clinical outcomes between the participants referred to physiotherapy in the control practices with participants self-referring in the intervention practices. We will also compare the self-referrers with those that do not self-refer within the intervention group.

The pilot data will provide information on the parameters needed for a realistic sample size calculation (mean, standard deviation and treatment effects of the primary outcome for the two arms) for a future, main cluster RCT. The intra-cluster correlation (ICC) will be calculated and compared with the estimates from previous large primary-care-based trials. However, as we only have 4 GP practices, we expect the estimated ICC to be unreliable given the likely wide confidence intervals. The non-inferiority margin will not be calculated from the pilot data as previous research in musculoskeletal disorders has estimated a minimal clinically important difference (MCID) from 2 to 4 points for the SF-36v2 Physical Component Summary (PCS) subscale which will be used to inform the non-inferiority margin of any future main trial [33–36].

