### Setting and clusters

The setting is primary care in England for adults with musculoskeletal problems (GP practices and linked NHS physiotherapy services). GP practices are the unit of randomisation, and thus, patients follow the care pathways to which the practice is randomised. In this pilot, RCT practices will be stratified only on practice size, but in a main trial, practices would also ideally be stratified by index of deprivation. Randomisation of GP practices will be undertaken by an independent statistician. GP practices will be randomised to one of two arms, either to continue with usual GP-led primary care for musculoskeletal patients with the addition of the offer of a self-referral physiotherapy pathway (intervention group) or to continue with usual GP-led primary care alone (usual care control group). Practices will be randomised according to a computer-generated random numbers stratified by the practice size (small or large) in the ratio 1:1. In a main study, we would plan to further stratify by practice setting and area level deprivation (through minimisation) in order to ensure balance in key practice characteristics in each arm of the trial.

GP practices are eligible to take part if they meet the following criteria: they are within the Vale Royal Clinical Commissioning Group area of Cheshire and the Clinical Research Network (CRN); they are a group practice, currently referring musculoskeletal patients to NHS physiotherapy services; they do not currently offer direct access to physiotherapy; and they are willing to test direct access. The balance between scientific considerations and the need for consent is a known issue for cluster trials [27]. Informed consent for practices to participate will be provided by the senior GP partner in each practice acting as ‘guardian’ for patients in their care. Patients will follow the care to which their practice is randomised with identical patient information for both arms providing general information about the study, explaining that their local musculoskeletal services are being evaluated using patient self-reported clinical outcomes and medical record review. Individual patients will therefore be able to opt out of data collection.

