#### Feasibility of study recruitment and retention

The number of participants identified and recruited using each recruitment method will be reported, along with the number of participants followed up at each time-point. Withdrawals (and where possible, reasons for withdrawals) will be reported. A priori, we have defined a success criterion of 40 % of the total number of participants invited to be recruited to the research evaluation. Whilst a retention rate of 100 % would be ideal, we will consider a rate of 70 % at 6 months follow-up satisfactory. We will provide the point estimate of the proportion and its 95 % confidence interval (CI). Difference in recruitment uptake rate and follow-up rates at each time-point will be compared between the intervention and control arms.

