As this is a pilot trial this will be an exploratory analysis, with the aim to inform the cost data collection and analysis of a future main larger trial. We will test our methods of collecting cost data, from patient questionnaires and medical record reviews and assess the completeness of the data collected. A cost-consequence analysis will be reported, describing all the important results relating to costs and consequences. Analyses will be mainly descriptive, and all costs and outcomes will be summarised using means and 95 % confidence intervals. The data for costs are likely to have a skewed distribution; therefore, the plan is to explore the nature of the distribution of costs. If the data is not normally distributed, a non-parametric comparison of means (e.g. bootstrapping) will be undertaken.

The base case cost analysis will adopt a NHS and personal social services (PSS) perspective. A broader costing perspective will be considered in a sensitivity analysis, taking into account NHS/PSS costs, patients’ personal expenditure and costs associated with work loss. The robustness of the results will be explored using sensitivity analysis and will explore uncertainties in the trial based data and any assumptions made in the base case analysis.

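### With two practices per arm, the mixed-model 95% CI is likely to be too narrow without a small-sample df correction and should not be called a credible range for the true difference

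*Protocol article*

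**What the plan says.** The number of clusters is plain. The Evidence of selection bias section opens: "Since this is a pilot trial with only four clusters randomised". Under Setting and clusters, practices are randomised by computer-generated numbers, "stratified by the practice size (small or large) in the ratio 1:1". That implies two practices per arm.

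Under Analyses of clinical outcomes, the SF-36v2 PCS is analysed with a mixed model that has "a random effect for the GP practices and will include a treatment-by-time interaction", giving an effect estimate at 2, 6 and 12 months. The model is to supply a two-sided 95% CI "to show a credible range for the true difference in the SF-36v2 PCS subscale between intervention and the control arms". No degrees-of-freedom method or small-sample correction is named. The section calls the clinical analyses exploratory and mainly descriptive and plays down p values, but does not extend that caution to the interval.

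The same section then says of the ICC: "as we only have 4 GP practices, we expect the estimated ICC to be unreliable given the likely wide confidence intervals". It plans to compare the pilot ICC with estimates from earlier large primary-care trials. It lists treatment effects among the parameters for sizing the main trial, and cites a minimal clinically important difference (MCID) of 2 to 4 PCS points.

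**The concern.** Arm is a practice-level factor, so the precision of the arm contrast is governed by variation between practices. The practice variance behind the ICC also drives the standard error of the treatment effect. The article treats that variance as untrustworthy when reporting the ICC, yet relies on it for an interval that it presents as the plausible range of the true difference.

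If the model is run in the usual large-sample way, with multiplier 1.96, two things go wrong. The multiplier takes no account of a variance estimated on 2 df. And when the practice variance is estimated as zero, the interval falls back to one that treats patients as independent.

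What is at stake is false precision in what is carried forward to the main trial. An uncorrected half-width of 2 to 4 points looks informative beside an MCID of 2 to 4 points. An interval that reflects four practices usually would not.

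**Working it through.** **The plan's own figures.** From the Sample size section: 100 consulters per month × 0.80 eligible × 0.50 responding = 40 per practice per month. Then 40 × 4 practices × 6 months = 960, and 960 × 0.80 = 768. Both reproduce. Per practice, 768 / 4 = 192.

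**Assumptions.** The article gives no ICC and no SD.
- ICC: 0.01 to 0.05 as the main range, with lower values also shown.
- SD: 10, because 2 points paired with an effect size of 0.2 gives 2 / 0.2 = 10. Pairing 4 points with 0.6 gives 4 / 0.6 = 6.7. (The effect sizes are in Design considerations and limitations.) Half-widths scale with the SD; coverage does not depend on it.

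**Degrees of freedom.** 4 practices − 2 arms = 2. The 97.5% point of t on 2 df is 4.303, and 4.303 / 1.960 = 2.20. For a standard error with 2 df, ±1.96 has coverage 1.96 / √(2 + 1.96²) = 1.96 / 2.417 = 81%. This is the limit as the ICC grows.

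**True standard error.** With two practices per arm, Var(difference) = V/2 + V/2 = V, where V = ICC × SD² + (1 − ICC) × SD² / 192.
- ICC 0.01: V = 1 + 99/192 = 1.516, SE = 1.23.
- ICC 0.05: V = 5 + 95/192 = 5.495, SE = 2.34.
- Patients treated as independent: 1.96 × 10 / √192 = ±1.41 points.

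**Chance that the practice variance is estimated as zero.** This is about 1 − exp(−1/λ), where λ is V divided by the within-practice part.
- ICC 0.01: λ = 1.516 / 0.516 = 2.94, probability 29%.
- ICC 0.05: λ = 5.495 / 0.495 = 11.1, probability 9%.

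**Simulation.** 400,000 trials per ICC, four balanced practices of 192, SD 10, one time-point:

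| ICC | True SE | REML coverage, 1.96 | Practice variance set to zero | Median half-width, 1.96 | Median half-width, t(2) |
|---|---|---|---|---|---|
| 0.001 | 0.79 | 95% | 57% | 1.5 | 3.2 |
| 0.005 | 1.01 | 91% | 40% | 1.7 | 3.6 |
| 0.01 | 1.23 | 88% | 29% | 2.0 | 4.4 |
| 0.03 | 1.87 | 84% | 13% | 3.1 | 6.7 |
| 0.05 | 2.34 | 82% | 9% | 3.8 | 8.4 |

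Both half-width columns use the REML standard error. Under maximum likelihood, coverage with 1.96 is lower: 82% at ICC 0.01 and 72% at 0.05.

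**Alternatives in the same simulation.**
- Practice-level means with t(2): 95.0% at every ICC.
- REML standard error with t(2): 99.6% at ICC 0.01, 96.9% at 0.05.
- REML with an adaptive Satterthwaite-type df: 93% to 94% for ICC 0.01 to 0.05.

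At SD 6.7, the medians for ICC 0.01 to 0.05 become about 1.3 to 2.6 points with 1.96 and 2.9 to 5.6 points with t(2).

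**The case against.** The strongest reply is that the article does not commit to a 1.96 interval, nor to REML or maximum likelihood. The df method is a detail that an analysis plan commonly settles. The Trial organisation and monitoring section mentions such a plan, and it is not shown here. With a suitable correction, the planned model covers adequately. This stands: the interval cannot be said to be certainly too narrow. What remains is the article's own wording, which promises a credible range from a variance that it describes as unreliable.

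A second reply is that the ICC is unknown. That also stands. At about 0.001 or less, the uncorrected REML interval covers about 95%.

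Third, a reader might infer that a too-narrow interval could appear to settle non-inferiority. The article does not support that. It plans no non-inferiority conclusion in the pilot, leaves the definitive test to the main trial, and does not derive the margin from pilot data.

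Fourth, a reader might extend the point to the recruitment and retention intervals ("We will provide the point estimate of the proportion and its" 95% CI) and to the costs, where for skewed data "a non-parametric comparison of means (e.g. bootstrapping) will be undertaken". Those sections do not mention practice, but neither do they specify a patient-level method. Silence in a condensed article is not an error. The 40% and 70% criteria are stated as rates and are not tied to a confidence limit.

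**Conclusion.** The point holds in conditional form. With two practices per arm, a mixed-model CI without a small-sample df correction is likely to be too narrow. At assumed ICCs of 0.01 to 0.05, a nominal 95% REML interval covers about 88% to 82%, and at a given standard error it is 2.2 times narrower than one using t(2). With the correction, the median half-width is about 4.4 to 8.4 points at SD 10, which says little against a 2 to 4 point MCID. Either way, the credible-range description is stronger than four practices can bear as the plan is written.

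These sizes rest on the assumed ICC and SD, equal practice sizes and a single time-point. Drift in practice effects over follow-up is not counted. The matter is moderate: the analysis is exploratory and the four-cluster limitation is openly acknowledged for the ICC. It still merits correction, because treatment effects are among the quantities to be passed to main-trial planning.

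**What to change.** 1. At each follow-up, adjust PCS at patient level for the listed covariates (age, area deprivation, widespread pain). Compare the adjusted practice means between arms with t on 2 df. Alternatively, keep the planned mixed model and name a small-sample df correction. The second route retains the repeated-measures handling of missing data. State whether practice size, the stratification factor, enters the analysis; adjusting for it would leave 1 df.
2. Add a sensitivity CI with the ICC fixed at the external primary-care estimates already to be consulted. With SD 10, 1.96 × true SE gives ±2.4 points at ICC 0.01 (1.96 × 1.23) and ±4.6 at 0.05 (1.96 × 2.34). This interval is conditional on the borrowed ICC and should be labelled so.
3. If neither form of item 1 is adopted, remove the credible-range wording and say that the interval does not reliably reflect between-practice variation.
4. Optionally, show recruitment, retention and cost results by practice.

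The cost is a few lines of code and text. The downside is visibly wider intervals that tell the reader little against the 2 to 4 point MCID.

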#### Missing outcome data

Since the primary outcome measure, physical health measured using the SF-36v2 PCS involves scoring individual items, we do not expect all returned questionnaires to have every item on the SF-36 completed. Based on the recommendation in the scoring manual [33], a scale score should be calculated if a respondent answers at least 50 % of the items in a scale. Missing data will be estimated by the average score, across completed items in the same scale for that respondent. If more than 50 % of the items in a scale are left blank, the imputation algorithm identifies the scale as ‘not computable’ and so the respondent is considered to have missing data for the SF-36v2 component scales.

In order to explore the extent and patterns of missing outcome data, we will report the proportion of missing values per item, proportion of participants who complete all items on the questionnaire and the proportion of respondents who answer at least 50 % of the items in a scale. The proportion of missing data will also be reported for the other key outcomes and compared between the participants from intervention and control practices. The characteristics of those lost to follow-up will also be compared with those who remain in the trial through follow-up.

#### Safety of direct access

Any possible cases of missed serious or significant pathology will be discussed within the study team. For any patient where there is evidence to suggest the physiotherapist failed to correctly identify this pathology when the patient directly accessed physiotherapy care and medical intervention was delayed will be reported.

#### Health economic analysis

The economic analysis will be exploratory, with the aim to inform the design of a full cost-utility analysis alongside a future main trial. A cost-consequence analysis will be reported, describing all the important results relating to costs and consequences for direct access to physiotherapy and usual care arms of the trial. Results will be presented from a health service perspective and a broader societal perspective taking into account patient-incurred costs and productivity losses. An exploratory willingness to pay (WTP) study [37] will also be conducted to assess the use of this methodology to measure broader benefits of direct access.

Data on costs will be sought from all participants and from a broad perspective, taking into account healthcare, patient and societal costs. Healthcare resource used will be collected using self-completed questionnaires at 6 and 12 months, with a recall period of 6 months in each. Questions will ask patients to recall GP consultations, visits to healthcare professionals, outpatient appointments, investigations or treatments and inpatient stays related to the index condition. Participants will be asked to distinguish between NHS and private practice visits. Resource used for the direct access pathway will be directly recorded and costs attached, staff time (taking into account any increased referrals to physiotherapy), materials (posters, flyers, referral forms) and training sessions. GP medical record review of all participants will provide data on relevant prescribed medications for all musculoskeletal problems. In addition, information on costs borne by the patient (e.g. over-the-counter medicines, devices) will be collected via the self-complete questionnaires. Productivity costs will take into account both absenteeism and presenteeism and will utilise self-report data on employment status, occupation and time off work and reduced productivity at work (presenteeism). As this is a pilot trial, the suitability of questions for collecting cost data directly from patients can be assessed, in order to ensure effective resource use and that cost data collection systems are established for a larger trial.

All patients will be asked to complete the 5-level version of the EuroQoL-5D (EQ-5D) questionnaire at baseline, 6 months and 12 months in order for the quality-adjusted life years (QALYs) over the 12-month time period to be calculated for each participant. The QALYs combine information on health-related quality of life and survival.

Resource use will be multiplied by unit costs obtained from standard sources (NHS Reference Costs, British National Formulary, Unit Costs of Health and Social Care) and healthcare providers. Due to the lack of nationally representative unit cost estimates for private healthcare, this care will be costed as the NHS equivalent in the base case. Patient reported costs for over-the-counter treatments will be used. Productivity costs will be calculated using data collected on employment status at every time-point and days off work due to their musculoskeletal problem. For those in paid employment, information on occupation and the nature of their employment (full time or part time) will be requested. The average wage for each respondent will be identified using UK Standard Occupational Classification coding and annual earnings data for each job type. The analysis will use the human capital approach, and the self-reported days of absence will be multiplied by the respondent-specific wage rate. The human capital approach assumes that the value of lost work is equal to the amount of resources an individual would have been paid to do that work and values productivity losses as a result of morbidity (or mortality) by measuring time lost from work and multiplying this with the gross wage of the person. Responses to the EQ-5D questionnaire at baseline and 6 and 12 months will be used to calculate QALYs for each participant using the area under the curve method.

As this is a pilot trial this will be an exploratory analysis, with the aim to inform the cost data collection and analysis of a future main larger trial. We will test our methods of collecting cost data, from patient questionnaires and medical record reviews and assess the completeness of the data collected. A cost-consequence analysis will be reported, describing all the important results relating to costs and consequences. Analyses will be mainly descriptive, and all costs and outcomes will be summarised using means and 95 % confidence intervals. The data for costs are likely to have a skewed distribution; therefore, the plan is to explore the nature of the distribution of costs. If the data is not normally distributed, a non-parametric comparison of means (e.g. bootstrapping) will be undertaken.

The base case cost analysis will adopt a NHS and personal social services (PSS) perspective. A broader costing perspective will be considered in a sensitivity analysis, taking into account NHS/PSS costs, patients’ personal expenditure and costs associated with work loss. The robustness of the results will be explored using sensitivity analysis and will explore uncertainties in the trial based data and any assumptions made in the base case analysis.

